## 8. APPENDIX 2: CONSUMER REPRESENTATIVE INVOLVEMENT AGREEMENT

### BACKGROUND

The TRAVel Vaccine Aids for Decision-making (TRAVAID) Project aims to develop evidence-based vaccine decision aids for travellers. We're using a mixed-methods approach to create decision aids for vaccine-preventable-diseases that involve complex decision-making processes. The success of this project hinges on tailoring these aids to user needs.

The role of TRAVAID Consumer Representatives is to contribute a consumer perspective at Steering Group meetings and advocate for consumer interests in the project's strategies and directions. Consumer Representatives are integral to this research, enhancing transparency and accountability. Your insights will ensure the research aligns with end-user perspectives and is relevant and impactful to the community.

Consumer Representatives are not employed or contracted by Monash University, however, as individuals involved and connected with the TRAVAID Project, we ask that you agree to certain conditions as outlined in this Agreement.

### ROLES & RESPONSIBILITIES

The responsibilities of Consumer Representatives include to:

- Attend monthly Steering Group Meetings and promptly notify the research team if unable to attend
- Share lived experiences appropriately and effectively
- Respect the views of other Steering Group members and foster open communication.
- Actively engage in review of study materials, and provide feedback to ensure that materials are accessible, understandable, relevant and respectful of the diverse needs of the travel community.
- Inform the research team about potential conflicts of interest
- Contact the research team if you have concerns or unresolved issues about your role or collaboration

The responsibilities of the research team include to:

- Provide regular updates to Consumer Representatives involved in the TRAVAID Project as agreed upon at the commencement of their working partnership
- Provide notice in advance, when feasible, for document review requests and/or other ad-hoc activities
- Ensure that Consumers involved in the project understand its purpose, process and designated roles
- Acknowledge and respect the expertise and lived experience of Consumers involved in the research project.

### CODE OF CONDUCT – BEHAVIOUR

Consumer representatives are expected to:

- Behave honestly and with integrity
- Act with due care and diligence
- Follow all applicable Australian laws
- Treat people equally and respectfully, regardless of culture, gender, age, or other features
- Encourage collaboration, communication and respect between members of the TRAVAID Steering Committee
- Participate in the activities outlined above

### PAYMENT

Consumer Panel members are offered an 'honorarium' (payment) as a gesture of appreciation.

Honorarium amounts are as follows:

- \$60 for each Steering Committee meeting participated in (for each meeting, of up to one hour in length; this is inclusive of any pre-meeting reading that is required).
- \$50 per hour for related activities such as providing feedback and comments on provided topics/papers.

These amounts reflect recommended practice when engaging consumer representatives as partners or advisers in health research. Consumer representatives will be given the option to accept the honorarium, or they can decline it; and there is no obligation on the consumer representative for future meetings whether or not they accept an honorarium for earlier participation. Honorarium amounts will increase by 2.5% every year.

Consumer Representatives will be able to choose how they would prefer to receive their honorarium (direct to bank account or voucher).

The honorarium payments are not subject to withholding tax or superannuation as there is no employer/employee between Consumer Representatives of the Steering Committee and the University. However, the ATO has indicated that payments may be subject to income tax in the recipient's hands where there is a connection to the recipient's income-producing activities (such as working in the health profession). We suggest that Consumer Representatives obtain their own taxation advice with regard to these payments.

## PRIVACY AND CONFIDENTIALITY

As a consumer representative, it's possible that you may see, hear or be given confidential information as part of your role. Please carefully read and complete the Privacy and Confidentiality Agreement for this study.

## TERMS

Please complete and return this form **only** if you agree with the following statements:

- I am participating as a consumer representative and am not legally obligated (i.e. contracted) to Monash University, the TRAVAID Project or any associated programs in regard to involvement.
- I will choose how regularly and how much I participate in any TRAVAID or associated program activities that I am invited to attend.
- I acknowledge that my involvement can be ended at any time, either by me or Monash University.
- I will be offered an honorarium (i.e. payment) as a gesture of appreciation for participation. The payment will not create any employee/employer relationship with the University and as such the University has no withholding or superannuation obligations in respect to the payment. I can choose to either accept or decline this honorarium with no impact on my participation. I understand that in certain circumstances (i.e. where there is a connection to my income-producing activities) that the payment may be considered taxable income and will seek my own advice on this matter.
- I am not a current student or staff member of Monash University and do not hold an adjunct appointment with the University.
- I am not entitled to an ABN as I am not carrying on an enterprise in Australia related to this research

## 10. APPENDIX 4: COMBINED SURVEY QUESTIONNAIRE (PRE-INTERVENTION, POST-INTERVENTION, FOLLOW-UP)

### JE Decision Aid RCT Pre-intervention Survey

## Questionnaire

### (Screening): Travel intentions

**These first questions are to find out if you're eligible for the study.**

Japanese encephalitis (JE) is a risk in 24 countries, shown on the map and listed below.

*NB: include a graphic of at-risk countries e.g. shaded map and country list*

Are you planning to spend time in any of these countries (outside of Australia) in the next six (6) months? Only include countries where you're planning to leave the airport.

|     |                   |
|-----|-------------------|
| Yes | [continue survey] |
| No  | [screen out]      |

**If Yes:** Please select the country where you plan to spend the most time from the drop-down list. If you will be spending equal time in more than one country, choose the country you will visit first. (required)

*NB: drop-down menu limited to JE-endemic areas excluding Australia*

### About you

**This next set of questions asks about you**

Which State or Territory do you currently live in? (please select from the list)

*NB: a drop-down list will be provided*

What is your age (in years)? (drop-down list: 18-100)

What is your gender?

|                                                 |                          |
|-------------------------------------------------|--------------------------|
| Female                                          |  |
| Male                                            |  |
| Non-binary/gender diverse                       |  |
| My gender identity isn't listed. I identify as: | [text box]               |
| Prefer not to say                               |  |

In which country were you born? (please select from the list)

*NB: a drop-down list of all possible options will be provided, with Australia pinned at the top*

Which country or countries were your parents or guardians born? (select all that apply)

- ☐ Australia
- ☐ China
- ☐ India
- ☐ Malaysia
- ☐ Philippines
- ☐ New Zealand
- ☐ South Africa
- ☐ United Kingdom (England, Scotland, Wales, Northern Ireland)
- ☐ Vietnam

627 ☐ Other, please specify

628

629

630 Do you speak a language other than English at home?

|                             |                          |
|-----------------------------|--------------------------|
| No – English only           |  |
| Yes – Other, please specify | [text box]               |

631

632 Are you of Aboriginal or Torres Strait Islander origin?

|                             |                          |
|-----------------------------|--------------------------|
| No                          |  |
| Yes, Aboriginal             |  |
| Yes, Torres Strait Islander |  |

633 *For people of both Aboriginal and Torres Strait Islander origin, mark both 'Yes' boxes*

634

635 What is the highest educational qualification you have completed?

|                                                 |                          |
|-------------------------------------------------|--------------------------|
| Year 11 or below                                |  |
| Year 12 or equivalent                           |  |
| Certificate (e.g. TAFE or trade certificate)    |  |
| Undergraduate degree (e.g. Bachelor's degree)   |  |
| Postgraduate degree (e.g. Master's degree, PhD) |  |

636

637 What is your current employment status?

|                                  |                          |
|----------------------------------|--------------------------|
| Employed full time               |  |
| Employed part time               |  |
| Employed casually/hourly         |  |
| In a family business without pay |  |
| Home maker                       |  |
| Student                          |  |
| Unpaid voluntary work            |  |
| Unemployed                       |  |
| Retired                          |  |

638

639 In general, would you say your health is?

|           |                          |
|-----------|--------------------------|
| Very good |  |
| Good      |  |
| Moderate  |  |
| Poor      |  |
| Very poor |  |

640

641 Are you currently pregnant?

|     |                          |
|-----|--------------------------|
| Yes |  |
| No  |  |

|                |                          |
|----------------|--------------------------|
| Not applicable |  |
|----------------|--------------------------|

642

643 Do you have any condition that weakens your immune system, or have you had any treatments  
644 (including medicines, chemotherapy or radiotherapy) in the past year that lower immune system  
645 function?

|     |                          |
|-----|--------------------------|
| Yes |  |
| No  |  |

646

647 Please tell us which condition(s) or treatment(s) affect your immune system. Select all that apply:

- 648 ☐ Leukaemia or lymphoma (blood cancer)  
649 ☐ Received an organ or stem cell transplant  
650 ☐ Living with HIV  
651 ☐ Taking steroids or immune-modulating medications (now or within last year)  
652 ☐ Receiving chemotherapy or radiotherapy (now or within last year)  
653 ☐ Other (please specify)

654

### 655 Health Literacy Assessment – the Single Item Literacy Screener

656 How often do you need to have someone help you when you read instructions, pamphlets, or other  
657 written material from your doctor or pharmacy?

- 658 ☐ Never  
659 ☐ Rarely  
660 ☐ Sometimes  
661 ☐ Often  
662 ☐ Always

663

664

### 665 Travel experiences

666

667 **You mentioned you'll be visiting a JE-risk area in the next 6 months. We'd now like to ask you**  
668 **some questions about your planned trip.**

669

670 How many countries do you plan to visit during this trip?

- 671 ☐ 1  
672 ☐ 2  
673 ☐ 3 or more

674

675 **If one:** Which country are you planning to visit during your upcoming trip? (Drop-down list – i.e.  
676 must select one only)

677 **If two:** What is the first country you are planning to visit during your upcoming trip? (Drop-down list)

678 **If two:** What is the second country you are planning to visit during your upcoming trip? (Drop-down  
679 list)

680 **If three:** What is the third country you are planning to visit during your upcoming trip? (Drop-down  
681 list)

682

683 When are you planning to start your trip?

- 684 ☐ November, 2024  
685 ☐ December, 2024  
686 ☐ January, 2025  
687 ☐ February, 2025  
688 ☐ March, 2025  
689 ☐ April, 2025  
690 ☐ May, 2025

691

692 How long do you plan to travel for?

- 693 ☐ less than one month  
694 ☐ 1 month or more

695

696 Where do you plan to spend the most time during your trip?

- 697 ☐ More than half my time in cities  
698 ☐ More than half my time in rural areas (areas with a lot of farms or forests)  
699 ☐ About the same amount of time in both cities and rural areas  
700 ☐ Not sure

701

702 Are you planning to consult a healthcare provider for travel health advice for this trip?

- 703 ☐ Yes, I'm planning to  
704 ☐ Yes, I've already done so  
705 ☐ No, I'm not planning to  
706 ☐ Not sure

707

708 If yes, where do you plan to get travel health advice from? (select all that apply)

- 709 ☐ General practitioner / primary care  
710 ☐ Travel medicine clinic  
711 ☐ Pharmacist  
712 ☐ Internet  
713 ☐ Friend or relative  
714 ☐ Travel agent  
715 ☐ Other, please specify

716

717 **This set of questions asks about your past travel experiences.**

718

719 Have you ever travelled overseas (outside of Australia)?

- 720 ☐ Yes  
721 ☐ No → skip to "How many overseas trips..."

722

723 In what year was your last overseas trip? \_\_\_\_\_ (Dropdown box: 2014 or earlier to 2024)

724

725 How many overseas trips have you taken in your lifetime? (select one only)

- 726 ☐ 1 or 2  
727 ☐ 3 or 4  
728 ☐ Between 5 and 10  
729 ☐ More than 10  
730 ☐ None → skip next 4 questions

731

732 Which of the following regions have you visited in your lifetime? (select all that apply):

- 733 ☐ Asia (excluding South Asia)

- 734 ☐ South Asia (India, Pakistan, Bangladesh, Nepal, Sri Lanka)
- 735 ☐ Africa
- 736 ☐ North America
- 737 ☐ Central and South America
- 738 ☐ Europe
- 739 ☐ Middle East
- 740 ☐ Oceania (New Zealand, Papua New Guinea, Pacific Islands)
- 741 ☐ Antarctica

742 *NB: More than one response can be selected (checkboxes)*

743

744 What were the reasons for your travel? (select all that apply)

- 745 ☐ Tourism (holiday)
- 746 ☐ Visiting friends and relatives
- 747 ☐ Business (e.g. meeting, conference)
- 748 ☐ Education (e.g. study abroad)
- 749 ☐ Other, please specify\_\_\_\_[text box]

750

751

## 752 Japanese encephalitis (JE)

753 **This next set of questions relate to your knowledge of Japanese encephalitis.**

754 Have you heard about JE before?

|                               |                          |
|-------------------------------|--------------------------|
| Yes                           |  |
| No → skip next question       |  |
| Not sure → skip next question |  |

755

756 Where did you hear about JE before? (Select all that apply)

|                                                                               |                          |
|-------------------------------------------------------------------------------|--------------------------|
| Internet                                                                      |  |
| General Practitioner (GP)                                                     |  |
| Other healthcare provider (e.g. nurse, pharmacist, specialist, travel clinic) |  |
| Family or Friends                                                             |  |
| In the news/media (e.g. TV, radio, newspaper)                                 |  |
| Employer                                                                      |  |
| Community leader or religious leader                                          |  |
| This study                                                                    |  |
| Not sure                                                                      |  |
| Other, please specify:                                                        |  |

757

758 Please review each of the following statements about Japanese encephalitis (JE) and tell us if you  
759 think they are true, false, or if you're not sure:

| Statements                                                                                             | True | False | Not sure |
|--------------------------------------------------------------------------------------------------------|------|-------|----------|
| You can catch JE from another person                                                                   |      | X     |          |
| JE is spread by mosquito bites                                                                         | X    |       |          |
| JE can be serious: some people may die from it, and some who survive will have long-term health issues | X    |       |          |
| There is a specific treatment that can help your body fight JE                                         |      | X     |          |
| JE can be prevented                                                                                    | X    |       |          |
| JE is caused by a bacteria                                                                             |      | X     |          |
| Most travellers to JE risk areas don't get JE                                                          | X    |       |          |
| Two vaccines for JE are available in Australia                                                         | X    |       |          |
| Avoiding mosquito bites can lower your risk of getting JE                                              | X    |       |          |

760 NB: Correct answers are indicated with red crosses

761

762

763 How concerned are you about getting JE on your upcoming trip?

- 764 ☐ Not at all concerned
- 765 ☐ A little concerned
- 766 ☐ Moderately concerned
- 767 ☐ Very concerned

768

769

## 770 Vaccines in general - Vaccine Confidence Index

771

772 The next group of questions asks about how you feel about vaccines in general.

773 To what extent do you agree with the following statements?

|                                               | Strongly disagree | Tend to disagree | Tend to agree | Strongly agree | Do not know |
|-----------------------------------------------|-------------------|------------------|---------------|----------------|-------------|
| Vaccines are important for people of all ages |                   |                  |               |                |             |
| Vaccines are safe                             |                   |                  |               |                |             |
| Vaccines are effective                        |                   |                  |               |                |             |
| Vaccines are compatible with my beliefs       |                   |                  |               |                |             |

## Vaccination for Japanese encephalitis (JE)

**This group of questions asks you specifically about JE vaccines.**

Have you **ever** had a conversation with a healthcare professional about Japanese encephalitis (JE) vaccines?

|          |                          |
|----------|--------------------------|
| Yes      |  |
| No       |  |
| Not sure |  |

Have you ever received a JE vaccine?

- ☐ No
- ☐ Yes → answer next two questions
- ☐ Not sure

If yes, Which JE vaccine did you receive?

- ☐ Imojev (live-attenuated)
- ☐ JEspect (inactivated) vaccine
- ☐ Not sure

If yes, How many doses did you receive?

- ☐ One dose
- ☐ Two doses
- ☐ Not sure

How important do you think getting a JE vaccine is for your health?

- ☐ Not at all important
- ☐ A little important
- ☐ Moderately important
- ☐ Very important

How safe do you think getting a JE vaccine is for you ?

- ☐ Not at all safe
- ☐ A little safe
- ☐ Moderately safe
- ☐ Very safe

How much do you trust the health workers who would give you a JE vaccine?

- ☐ Not at all
- ☐ A little
- ☐ Moderately
- ☐ Very much

Do you think most of your close family and friends would want you to get a JE vaccine?

- ☐ No
- ☐ Yes

818 Do you know where to go to get a JE vaccine for yourself?

819 ☐ No

820 ☐ Yes

821

822 How easy is it to pay for JE vaccination? When you think about the cost, please consider the cost of  
823 the vaccine (up to \$300), would you say...

824 ☐ Not at all easy

825 ☐ A little easy

826 ☐ Moderately easy

827 ☐ Very easy

828

829 How easy is it for you to pay for other costs associated with JE vaccination? (e.g., any payments to  
830 the clinic, the cost of getting there and the cost of taking time away from work)

831 ☐ Not at all easy

832 ☐ A little easy

833 ☐ Moderately easy

834 ☐ Very easy

835

836

837 Do you want to get a JE vaccine before your upcoming trip?

838 ☐ No, I do not want to

839 ☐ Yes, I do want to

840 ☐ I am not sure

841 ☐ I am already vaccinated

842

843 **Based on your choice for your upcoming trip, please answer the following questions:**

844

|                                                                 | Strongly Agree | Agree | Neither Agree nor Disagree | Disagree | Strongly Disagree |
|-----------------------------------------------------------------|----------------|-------|----------------------------|----------|-------------------|
| I know which options are available to me                        |                |       |                            |          |                   |
| I know the benefits of each option                              |                |       |                            |          |                   |
| I know the risks and side effects of each option                |                |       |                            |          |                   |
| I am clear about which benefits matter most to me               |                |       |                            |          |                   |
| I am clear about which risks and side effects matter most to me |                |       |                            |          |                   |
| I am clear about which is more important to me                  |                |       |                            |          |                   |

|                                                    |  |  |  |  |  |
|----------------------------------------------------|--|--|--|--|--|
| (the benefits or the risks and side effects)       |  |  |  |  |  |
| I have enough support from others to make a choice |  |  |  |  |  |
| I am choosing without pressure from others         |  |  |  |  |  |
| I have enough advice to make a choice              |  |  |  |  |  |
| I am clear about the best choice for me            |  |  |  |  |  |
| I feel sure about what to choose                   |  |  |  |  |  |
| This decision is easy for me to make               |  |  |  |  |  |
| I feel I have made an informed choice              |  |  |  |  |  |
| My decision shows what is important to me          |  |  |  |  |  |
| I expect to stick with my decision                 |  |  |  |  |  |
| I am satisfied with my decision                    |  |  |  |  |  |

845

846

[Pre-intervention exit page script](#)

---

**Important instructions for the Next Step**

Now, we'd like you to review some information about JE and JE vaccines. You will be randomly assigned to review either a JE fact sheet or the JE decision aid. Please follow these steps:

1. **Click here** to open your assigned material in a new window.
2. **Keep this survey open in the current window** so you can easily return after your review
  - a. If you're assigned the **fact sheet**, please scroll all the way to the bottom to access all the information
  - b. If you're assigned the **decision aid**, please make sure you complete all four steps.
3. **Take your time to review the information at your own pace.** We estimate this will take around 10-15 minutes.
4. **Once you've finished, please return to this window to finish the survey**

Have you followed all of the steps above?

☐ Yes

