## 138 **4. STUDY DESIGN**

139 This study will use an individually randomised, single-blinded, controlled trial design. Prospective  
140 Australian overseas travellers will be recruited through a consumer panel provider to participate in  
141 the trial.

142 Participation in the trial will involve three steps, plus an optional follow up. Participants will first  
143 complete an initial (pre-intervention) survey (Step 1). They will then be randomly assigned to either  
144 the intervention or control group and receive a link to the corresponding materials based on their  
145 group assignment. Participants will be instructed to keep the REDCap survey open in a separate  
146 browser tab while reviewing the assigned materials (Step 2). After reviewing the materials, they will  
147 return to the REDCap browser to complete a post-intervention survey (Step 3). Participants who  
148 complete Step 1 but do not commence Step 3 will be sent up to two invitational reminders via email  
149 between 48-72hrs after completion of Step 1. Additionally, participants will be asked to consent to  
150 be contacted 3-6 months after the initial survey to complete an optional follow-up survey. This  
151 follow-up will investigate whether they undertook travel and received JE vaccine. Participants may  
152 opt out of this follow-up contact if they choose.

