## **4.2. CONTROL ARM**

Participants randomised to the control arm will receive a link to an online health information page about JE managed by Healthdirect Australia. As the national virtual public health information service, Healthdirect Australia collaborates with federal, state and territory governments to provide a range of evidence-based health resources. Their platform features over 2,000 evidence-based and clinically safe pages of information.

The Healthdirect Australia JE webpage provides information on JE, including its geographic distribution, modes of transmission, symptoms and severity. It also covers preventive options, including mosquito bite avoidance and vaccines available in Australia.

The information is organised into a single, continuous webpage, with key details broken down into sub-section. The page includes tools for symptom checking and finding local health services, as well as accessibility features such as text enlargement, page-masking and text-to-speech capabilities.

A print to PDF function is available at the top of the page, and links to additional resources and support are also included. Users are informed that reading the page in full takes approximately 11-minutes.

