### 5.3. DETAILS OF PARTICIPANT INVOLVEMENT

Participation in the trial involves three steps, all completed in a single web-based session (Figure 1):

- Step 1: Pre-intervention survey (approximately 7-10 minutes): all participants will complete the same survey
- Step 2: Review of assigned information (approximately 15 minutes): participants will be randomised to review either the JEVaDA tool (intervention) or the Healthdirect JE page (control)

Figure 1: Flowchart of Participant Involvement

[figure not shown]

- Step 3: Post-intervention survey (approximately 5 minutes): all participants will complete the same survey

Participants who complete both the pre- and post-intervention surveys will be considered to have provided complete responses. The total estimated time commitment is up to 30 minutes.

Participants will also be asked to consent to a follow-up contact 3-6 months after the initial survey for an optional follow-up survey. This follow-up will assess whether they travelled and received the JE vaccine. Participants can choose to opt out of this follow-up contact. Those who do not opt out will be asked to complete a brief (5 minute) follow-up survey 3-6-months post-intervention.

Since this trial is conducted online, participants must have access to an internet connection in order to participate.

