**Proceed**

895 **Questionnaire**

---

896

897 **Decision Aid / Fact Sheet**

898 **This set of questions relates to your experience with the resource you were assigned to review**

899 Which resource were you assigned to review?

- 900 ☐ JE decision aid website – next five questions appear
- 901 ☐ Health Direct JE fact sheet – next two questions only

902 Did you review the resource?

- 903 ☐ Yes, the whole resource
- 904 ☐ Yes, only part of it
- 905 ☐ No, I didn't review it

906 Please estimate the amount of time you spent reviewing this information (in minutes): \_\_\_\_

907 *NB: Text validation applied to ensure only whole numbers can be inputted*

908 The length of the decision aid was:

- 909 ☐ Too long
- 910 ☐ Too short
- 911 ☐ Just right

912 I found the decision aid was:

- 913 ☐ Slanted towards alternatives to vaccination
- 914 ☐ Slanted towards vaccination
- 915 ☐ Balanced

916 The amount of information was:

- 917 ☐ Too much
- 918 ☐ Too little
- 919 ☐ Just right

920 Please tell us your thoughts on the decision aid. What did you like, what didn't you like, and how can we improve it? \_\_\_\_ (free text, optional)

922 **Japanese encephalitis (JE)**

923 **This next set of questions relate to your knowledge of Japanese encephalitis.**

924 Please review each of the following statements about Japanese encephalitis (JE) and tell us if you think they are true, false, or if you're unsure:

| Statements                           | True | False | Unsure |
|--------------------------------------|------|-------|--------|
| You can catch JE from another person |      | X     |        |

|                                                                                                        |   |   |  |
|--------------------------------------------------------------------------------------------------------|---|---|--|
| JE is spread by mosquito bites                                                                         | X |   |  |
| JE can be serious: some people may die from it, and some who survive will have long-term health issues | X |   |  |
| There is a specific treatment that can help your body fight JE                                         |   | X |  |
| JE can be prevented                                                                                    | X |   |  |
| JE is caused by a bacteria                                                                             |   | X |  |

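### The post-intervention JE knowledge test can be answered with the assigned resource still open, so secondary outcome 1 may mix knowledge with look-up

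*Combined protocol and SAP*

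**What the plan says.** The exit page script in Appendix 4 sets out the sequence. Participants click "to open your assigned material in a new window", are told "Keep this survey open in the current window", and on finishing are asked to "return to this window to finish the survey". Protocol section 4 describes the same arrangement with browser tabs: "Participants will be instructed to keep the REDCap survey open in a separate" tab while they review the material. Section 5.3 adds: "Participation in the trial involves three steps, all completed in a single web-based session".

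The post-intervention survey opens with a few questions about the resource. The nine knowledge statements follow, under the stem "Please review each of the following statements about Japanese encephalitis (JE) and tell us if you think they are true", false, or if they are unsure. The same nine items are asked in the pre-intervention survey, before any material is supplied.

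SAP section 2.8 counts the correct post-intervention answers and compares arms by Poisson regression, adjusted for the pre-intervention score, age and sex. It plans no sensitivity analysis for look-up.

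On layout, protocol section 4.2 says of the control page: "The information is organised into a single, continuous webpage". Section 4.1 describes JEVaDA as a stepwise tool in three main sections. Both resources offer a PDF. Section 5.7.2 says the knowledge items were developed from the decision aid's content and from the literature.

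**The concern.** Secondary outcome 1 asks which resource leaves travellers knowing more about JE. A participant who returns to the survey with the resource window still open can check a statement before answering it. The survey neither discourages this nor asks about it, and the documents describe no time limit or page-focus check. The pre and post tests are then taken under different conditions, and the post score measures knowledge plus retrieval.

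The protocol recognises a related threat elsewhere: section 5.7.1 places the Decisional Conflict Scale immediately after the intervention partly so that information-seeking does not confound it. The knowledge test, which has right answers to find, has no comparable protection.

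Two consequences are possible. If look-up is equally common in both arms, a true difference shrinks. If it is unequal, the comparison is biased, and the bias can favour either arm.

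**Working it through.** **1. The plan's own figure.** The only power statement (protocol 5.11, SAP 2.5) concerns the primary outcome: effect size 0.30, pre-post correlation 0.5, two-sided alpha 0.05, 175 per group. The residual SD is sqrt(1 - 0.5²) = 0.866. Power is then 0.8998 at 175 per group, and 176 per group are needed for 90%. 350/(1 - 0.30) = 500. The stated figures reproduce to rounding. The scale is self-rated and has no answers to look up, so this calculation is untouched. No power is stated for knowledge.

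**2. Inputs for the illustration, all assumed.** Mean correct without look-up is 7.0 of 9 (JEVaDA) and 6.5 (control), the SD is 1.6 and the pre-post correlation 0.4. Anyone who looks up scores 9, and the SD is held fixed. Only the 175 per arm comes from the SAP.

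**3. Formula.** With look-up proportions a (JEVaDA) and c (control):

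Difference = [7.0(1 - a) + 9a] - [6.5(1 - c) + 9c] = 0.50 + 2.0a - 2.5c.

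SE = 1.6 × sqrt(1 - 0.4²) × sqrt(2/175) = 0.157. Approximate power = Φ(difference/SE - 1.96). This is a linear-model approximation, not the planned Poisson model.

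| Look-up, JEVaDA | Look-up, control | Difference (items) | Approximate power |
|---|---|---|---|
| 0% | 0% | 0.50 | 89% |
| 20% | 20% | 0.40 | 72% |
| 30% | 30% | 0.35 | 61% |
| 10% | 30% | 7.20 - 7.25 = -0.05 | effect gone |
| 30% | 10% | 7.60 - 6.75 = +0.85 | effect inflated |

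**4. Cross-check with a different look-up model.** Let p be the true proportion correct, and suppose a share L of the items not known is looked up and corrected. The observed proportion is p + (1 - p)L. Ratios below are JEVaDA over control; SAP Table 5 labels JEVaDA as the reference, so a ratio reported that way would be the inverse.

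- Equal look-up, true 0.70 against 0.60: the ratio is 1.17 with no look-up, 0.76/0.68 = 1.12 at L = 20%, and 0.85/0.80 = 1.06 at L = 50%.
- No true difference, look-up 20% in control and 10% in JEVaDA: at p = 0.5 the proportions are 0.55 and 0.60 (JEVaDA first), or -0.45 items and a ratio of 0.92. At p = 0.8 they are 0.82 and 0.84, or -0.18 items and 0.98. Swapping the arms reverses the sign.
- In that second case, with 175 per arm and an assumed score SD of 2 items, a significant result would appear in about 13% (p = 0.8) to 56% (p = 0.5) of trials.
- With equal look-up and no true difference the ratio stays at 1.00.

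**The case against.** The strongest reply is that the documents never say the resource stays open or is consulted. The instruction is to keep the survey open, and the sequence is review, finish, return. Some participants will close the material. Those who come back only after the reminders at 48 to 72 hours (protocol section 4) may no longer have it to hand. Section 5.5 bases points on survey length and mentions none for correct answers, and an unsure option is offered, so no motive for look-up is shown. All of this stands. A reader might infer that the post-test is in fact taken open-book, but the text supports only that it can be.

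A reader might also infer that look-up is easier on the single Healthdirect page, so that the comparison is biased against JEVaDA. The documents do not support that either. One continuous page may be quicker to scan, but the items were built partly on JEVaDA's content, JEVaDA has a condensed PDF, and the control page can also be saved as a PDF. Nothing shows that the control page answers all nine items. The direction is open.

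The absence of a safeguard can be asserted only for the visible text. Printed line numbers in Appendix 4 jump from 846 to 895 with only the short exit script between, so introductory wording to the post-survey may have been removed from the copy reviewed.

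Finally, this is one secondary outcome with no stated power. That limits the weight of the point but does not remove it.

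**Conclusion.** The point holds as a limited one. As written, the procedure allows an open-book post-test of knowledge against a baseline taken without any resource, and the visible wording does nothing to discourage it. Equal look-up causes no bias when there is no true difference, but it dilutes a real one: 0.50 items becomes 0.40 at 20% and 0.35 at 30%. Unequal look-up can push the result either way, from -0.05 to +0.85 items around a true 0.50 in the two mirror-image scenarios. These sizes rest entirely on assumed means, SD, correlation and look-up rates, and on look-up giving full marks. They show sensitivity and are not estimates of what happened. The point is worth acting on mainly because the remedy costs almost nothing.

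**What to change.** Change step 4 of the exit page to: *Once you've finished, please close the window with the information, then return here to finish the survey.* At the head of the post-intervention knowledge block add: *Please answer from memory, without looking back at the information.* Use identical wording in both arms. The cost is two sentences and a minor ethics amendment, with no extra participants or staff. The small downside is that compliance cannot be enforced online.

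This may come too late for the present trial. The follow-up survey looks back to late 2024, and SAP section 3 describes the March 2025 version as final before data analysis. If collection is complete, describe secondary outcome 1 as knowledge measured with the resource potentially available, state that the visible instructions did not guard against look-up (after checking the full survey build), and interpret the incidence rate ratio with that limitation, including the possibility that a small or null ratio reflects dilution. The wording can then be used in later TRAVAID decision-aid evaluations.
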